**FIGURE 4 F4:**
[figure not shown]
Adverse event management flowchart.

##### Safety analysis

2.9.3.4

Adverse events will be analyzed using standardized evaluation scales. An independent Safety Committee (SC) will be established, composed of five members with no conflicts of interest: a principal investigator, an acupuncture clinician, a rehabilitation medicine specialist, a statistician, and a patient representative from the stroke rehabilitation community. The SC will be responsible for reviewing and evaluating all safety data and adverse events collected during the trial. Its specific duties will include assessing cumulative serious adverse event (SAE) reports, verifying entries in the Immediate AE Record Form within 24 h, conducting routine reviews every 2 months, and performing expedited reviews of any SAE within 48 h to ensure trial integrity and protect participants’ rights and health. For statistical analysis, Fisher’s exact test will be employed for categorical data comparisons, while the Kruskal-Wallis H test will be utilized for analyzing ordinal categorical variables.

##### Scope of adverse event reporting

2.9.3.5

In accordance with the CIOMS Guidelines for Adverse Event Reporting (45), this study will comprehensively collect and report all adverse events (AEs). The reporting will include the frequency, severity, and potential relationship to the intervention for every documented AE, thereby ensuring a complete representation of participant safety exposure throughout the trial period.

### Evaluation schedule

2.10

FOIS, NIHSS, SWAL-QOL, PAS, and YPR-SRS will be assessed at baseline (pre-treatment), 15 and 30 days after treatment initiation, and 30 and 60 days post-treatment completion. Additionally, fMRI-derived ReHo and ALFF metrics, sEMG evaluations, and PRO scores will be obtained at baseline and at 15 and 30 days following treatment initiation. The study timeline for enrollment, intervention, and assessment is detailed in Table 4. All dropouts and their respective reasons will be systematically documented in the case report forms (CRFs).

**TABLE 4 T4:** Study assessment schedule.

Times outcomes	Before treatment	Treatment				Follow-up	
	Day 3–0	Week 1–2	(Day 15)	Week 2–4	(Day 30)	Day 60	Day 90
**Basic medical history collection**							
Informed consent	×						
Basic information	×						
Medical and previous treatment	×						
Complications and its treatment	×						
Location of cerebral infarction	×						
Inclusion/exclusion	×						
Randomization	×						
**Interventions**							
Acupuncture		×		×			
Swallowing rehabilitation training		×		×			
**Assessment**							
FOIS	×		×		×	×	×
ReHo	×		×		×		
ALFF	×		×		×		
sEMG	×		×		×		
PAS	×		×		×	×	×
YPR-SRS	×		×		×	×	×
SWAL-QOL	×		×		×	×	×
NHISS	×		×		×	×	×
PRO	×		×		×		
TEX-Q	×						
**Adverse events observation**							
AE	×^→^						

### Statistical analysis

2.12

#### Functional imaging evaluation indicators

2.12.1

Statistical analysis is performed using the DPABI V5.1^3^ software package. Whole-Brain Analysis: Paired *t*-tests will be used to compare pre- and post-intervention ALFF, fALFF, ReHo, and FC values within each group (acupuncture and rehabilitation training), as well as between groups after intervention. Based on prior evidence indicating direction-specific neuromodulation by acupuncture in swallowing networks (47, 48), the resulting statistical maps will be corrected using one-tailed Gaussian random field theory (voxel *p* < 0.01, cluster *p* < 0.05). ROI Analysis: Mean ReHo and ALFF values will be extracted from each ROI and analyzed using repeated-measures ANOVA to assess within-group changes over time and between-group differences.

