### Objective

2.1

This study aims to explore acupuncture’s efficacy in post-stroke dysphagia (PSD) patients, clarify the neural mechanisms of acupuncture intervention for PSD, and obtain high-quality evidence.

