##### Recovery of the swallowing center and peripheral nerves

2.9.2.1

(1) fMRI data acquisition and analysis

Functional magnetic resonance imaging (fMRI) will be acquired to measure ReHo and ALFF indicators, which will be assessed before and during treatment. The ReHo indicator quantifies local neural activity synchronization, with changes indicating functional reorganization at the regional level (28). The ALFF metric reflects spontaneous neural activity intensity, thereby indicating the dynamic changes in brain functional reorganization (29).

Structural images are obtained using a TI-3D MPRAGE sequence with a sagittal scan orientation (left-to-right acquisition), yielding high-resolution T1-weighted images of the whole brain. Scan parameters are: repetition time (TR)/echo time (TE) = 2,000 ms/1.97 ms; flip angle (FA) = 8°; number of excitations (NEX) = 0.5; field of view (FOV) = 256 × 256 mm; matrix size = 256 × 256; slice thickness = 1.0 mm; no gap; 192 slices; scan time = 4 min 40 s; total images = 190.

Resting-state fMRI (rs-fMRI) data are acquired using a gradient-echo (GRE) single-shot echo-planar imaging (EPI) sequence. Scan parameters are: TR/TE = 2,000 ms/30 ms; FA = 90°; FOV = 220 × 220 mm; matrix = 64 × 64; slice thickness = 3 mm; gap = 3 mm; 37 slices; 240 time points; scan time = 8 min 8 s; producing 2,037 volumes.

Functional MRI data will undergo a standardized preprocessing pipeline. First, DICOM images will be converted to NIfTI format, followed by the exclusion of participants exhibiting excessive head motion—defined as translation exceeding 2 mm or rotation > 2°—or signal artifacts. Subsequent core preprocessing will include realignment for motion correction, slice timing adjustment, spatial normalization to the MNI152 template at 2 mm^3^ isotropic resolution, nuisance regression incorporating six head motion parameters along with cerebrospinal fluid and white matter signals, and band-pass filtering between 0.01 and 0.08 Hz. Finally, spatial smoothing will be applied using a 6 mm full-width-at-half-maximum Gaussian kernel.

Regions of interest (ROIs) will be defined based on the Automated Anatomical Labeling (AAL) atlas (30). In accordance with previous neuroimaging studies on swallowing mechanisms (31), the ROIs will include the precentral gyrus, insula, and anterior cingulate cortex.

(2) Surface electromyography (sEMG) detection

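### Section 2.12.1 lists within-arm imaging change beside the between-arm difference, tests two metrics that are not outcomes, and describes no error control across tests, so a mechanistic claim need not rest on the randomised contrast

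*Protocol article*

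**What the plan says.** Section 2.1 makes it an aim to "clarify the neural mechanisms of acupuncture intervention for PSD, and obtain high-quality evidence". Section 2.12.1 holds the imaging analysis.

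- **Whole brain.** Paired t-tests on four metrics are planned "to compare pre- and post-intervention ALFF, fALFF, ReHo, and FC values within each group (acupuncture and rehabilitation training), as well as between groups", the between-group comparison being on values after intervention. The maps are to be "corrected using one-tailed Gaussian random field theory (voxel *p* < 0.01, cluster *p* < 0.05").
- **Regions.** Mean ReHo and ALFF per region are "analyzed using repeated-measures ANOVA to assess within-group changes over time and between-group differences". Section 2.9.2.1 fixes the regions: "the ROIs will include the precentral gyrus, insula, and anterior cingulate cortex". No significance level is given for these tests.
- **Outcomes.** The abstract, section 2.9.2.1, section 2.10 and Table 4 name ReHo and ALFF as the imaging measures. Section 2.10 states that "fMRI-derived ReHo and ALFF metrics, sEMG evaluations, and PRO scores will be obtained at baseline" and again at days 15 and 30. fALFF and FC appear only in section 2.12.1.
- **Multiplicity.** The only adjustment across tests in the article is the Bonferroni correction for subgroups in section 2.12.6, where the results are also labelled exploratory. Section 2.12.1 carries no such label.

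**The concern.** Randomisation protects only the comparison between arms. Section 2.3 admits patients 15 to 180 days after stroke, and section 2.8 gives all of them standard stroke treatment. A change from the first to the last scan within the acupuncture arm therefore mixes any effect of needling with spontaneous recovery, background care and repeat scanning, all of which the rehabilitation arm shares. Section 2.12.1 lists this change alongside the between-arm difference, both for the maps and for the regions, and does not say which of them supports a conclusion on mechanism.

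The whole-brain between-arm comparison is also set on values after intervention. It is a randomised comparison, but it leaves the baseline scan unused and carries any baseline difference between the arms into the result. At map level, no between-arm comparison of change is specified.

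At stake is the trial's second aim. A cluster or region that changes in the acupuncture arm could be reported as the mechanism of acupuncture when both arms changed alike. It could also be one of many tests that crossed its threshold by chance, possibly on a metric never declared as an outcome.

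**Working it through.** **Inputs.** Four whole-brain metrics, three comparisons per metric and cluster p < 0.05 per map (2.12.1); three regions (2.9.2.1) and two regional metrics (2.12.1); 40 evaluable patients per arm (2.7). Assumed: a 0.05 level for the regional tests, left and right pooled within a region, and equal correlation r between tests of 0 to 0.7.

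**1. The plan's own sample size.** The article gives no imaging sample size. The 40 per arm is for FOIS and reproduces with a one-sided test: 2 × 1.09² × (1.645 + 0.842)² / (1.31 − 0.31 − 0.39)² = 14.69 / 0.372 = 39.5, so 40. Then 40 / 0.8 = 50 per arm, 100 in all. I use 40 as the number scanned. Head-motion exclusions (2.9.2.1) could lower it.

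**2. Count of tests.** Maps: 4 × 3 = 12, of which 8 are within-arm and 4 between-arm. Regions: 3 × 2 = 6. Total 18. Between-arm only: 4 + 6 = 10.

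**3. Chance of at least one false positive, no true effect.** If independent, this is 1 − 0.95^K. K = 6 gives 0.265 and K = 10 gives 0.401. For correlated tests I integrated over a shared normal factor u. One-sided: 1 − ∫ Φ((1.645 − √r·u)/√(1−r))^K φ(u) du. The two-sided version uses ±1.96.

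| Tests | r = 0 | r = 0.3 | r = 0.5 | r = 0.7 |
|---|---|---|---|---|
| 6, one-sided / two-sided | 0.26 | 0.22 / 0.24 | 0.19 / 0.21 | 0.15 / 0.16 |
| 10, one-sided / two-sided | 0.40 | 0.31 / 0.35 | 0.25 / 0.29 | 0.19 / 0.21 |
| 18, one-sided / two-sided | 0.60 | 0.42 / 0.51 | 0.33 / 0.40 | 0.23 / 0.28 |

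The smallest entry is three times 0.05. The random field correction does not lower these figures, because it already sets the 0.05 for each map.

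**4. Within-arm change when the arms do not differ.** Suppose both arms share the same true change of d standard deviations of the paired difference, with 40 scanned per arm. The chance p that one arm's pre/post test is significant at one-sided 5% comes from the noncentral t with 39 degrees of freedom and noncentrality d√40. The chance of acupuncture significant and rehabilitation not is p(1 − p).

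| d (assumed) | 0.1 | 0.2 | 0.3 | 0.4 | 0.5 | 0.6 |
|---|---|---|---|---|---|---|
| p, one arm | 0.15 | 0.34 | 0.59 | 0.80 | 0.93 | 0.98 |
| p(1 − p) | 0.13 | 0.23 | 0.24 | 0.16 | 0.07 | 0.02 |

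This is a single t-test and stands in for the principle. It is neither a cluster-thresholded map nor the planned ANOVA. The first row matters most: the larger the shared recovery, the more surely the acupuncture arm shows a significant change with no difference between arms.

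**5. Outcome list against analysis list.** Outcomes: ReHo, ALFF. Whole-brain analysis: ALFF, fALFF, ReHo, FC. Half of the whole-brain metrics are undeclared.

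**The case against.** Imaging is a secondary outcome, and a condensed article may leave multiplicity and the ranking of secondary tests to a full protocol or SAP that is not shown. That is a fair limit: the mere absence of a multiplicity procedure would not be a finding. What stands is what the article does fix, namely the per-map threshold, the within-arm tests listed beside the between-arm ones, the post-only map comparison, and two metrics that contradict its own outcome list.

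Four stronger readings are tempting, and the documents do not support them.

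- A reader might infer that no comparison addresses mechanism at all. Section 2.12.1 does name between-group comparisons, and a two-arm repeated-measures ANOVA ordinarily contains a group-by-time term. What is lacking is priority for that term. Nor does the article say that a within-arm change would establish mechanism; it leaves that open.
- A reader might infer that a false mechanistic finding is more likely than not. That needs all 18 tests and near independence (0.60 at r = 0); at r = 0.5 the figure is 0.33-0.40. The 0.05 level for the regional tests is itself inferred.
- A reader might infer that the day-15 scan doubles the maps. The abstract places day 15 during treatment, so day 30 is the natural post-intervention scan. Day 15 fits the regional ANOVA as a further time level.
- A reader might infer that about a quarter of null trials would show change in the acupuncture arm only. The 0.24 at 0.3 SD is close to the ceiling of 0.25 for p(1 − p); over 0.1-0.6 SD the range is 0.02-0.24.

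**Conclusion.** The point holds as a defect in which comparisons carry weight and in how they are labelled. Followed as written, section 2.12.1 lets within-arm change, which includes shared recovery, be read as a mechanism of acupuncture; it compares the arms at map level on post-intervention values only; and it tests fALFF and FC without declaring them. With no error control described across tests, the chance of at least one false positive is several times 5%: about 0.15-0.26 for the six regional tests and 0.19-0.40 for the ten between-arm tests.

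These ranges rest on an inferred 0.05 level for the regional tests, pooled hemispheres, and assumed correlations from 0.7 down to 0. The objection to within-arm change does not depend on them, since it follows from the design. The primary FOIS analysis is untouched. The change should be made before imaging results are interpreted.

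**What to change.** In section 2.12.1:

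1. Name the between-arm group-by-time contrast, baseline to day 30, for ReHo and ALFF in the three listed regions as the analysis that supports a conclusion on mechanism, with Holm correction over the six tests.
2. Label all within-arm pre/post tests descriptive and all whole-brain maps exploratory.
3. Mark fALFF and FC exploratory or delete them, so that the analysis matches the abstract, 2.9.2.1, 2.10 and Table 4.

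This is wording and one adjustment step, with no new scans. The cost is power per region. The strictest Holm level is 0.05 / 6 = 0.0083 (two-sided critical value 2.64 against 1.96). An effect with 80% power at 0.05 has a standardised mean of 1.96 + 0.84 = 2.80, so at that level its power is Φ(2.80 − 2.64), about 56%. Later Holm steps are less strict. Within-arm maps could also no longer be cited as evidence of mechanism.

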### Study design

2.2

This is a multicenter, open-label, randomized controlled trial. A total of 115 participants will be enrolled, including 100 PSD patients to be randomly allocated in a 1:1 ratio to either the experimental group or the rehabilitation control group, and 15 additional participants will serve as the healthy control group. The study period will include baseline observations and 4 weeks of treatment. The clinical efficacy of acupuncture intervention will be assessed using functional assessment scales on day 15, day 30 during treatment, and at 30 and 60-day follow-ups after treatment completion.

This clinical trial adheres to the Consolidated Standards of Reporting Trials (CONSORT) guidelines (12) and complies with the Standards for Reporting Interventions in Clinical Trials of Acupuncture (STRICTA) (13) to ensure methodological rigor in acupuncture-specific interventions. The study design flowchart is presented in Figure 1.

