### Sample size, randomization, and blinding

2.7

The primary efficacy outcome is the FOIS score. As neither our team nor previous studies have used this measure to assess acupuncture efficacy for post-stroke dysphagia, it is not possible to determine an appropriate effect size from existing data. A review of similar studies has revealed that after 4 weeks, the FOIS score difference from baseline was 1.31 (rehabilitation training group) vs. 0.31 (sham training group), with a standard deviation of 1.09 (16). This value will be used as the expected effect size for this trial, and sample size calculations will be conducted based on a superiority trial design (17). These parameters (μA = 1.31, μB = 0.31, σ = 1.09, α = 0.05, power = 0.8, δ = 0.39) were applied in a superiority design with 1:1 allocation. After calculation, nA = nB = 40. Considering a 20% dropout rate, this study is expected to enroll 100 patients.

Randomization will use computer-generated numbers to allocate patients equally to acupuncture or rehabilitation groups. A stratified block randomization design will be employed. An independent statistician will generate all random sequences in SPSS 25.0, with study center and baseline FOIS as stratification factors, block lengths of 4 and 6 randomly interleaved, and the seed number set to 20240420. Allocation concealment will be implemented through sequentially numbered, opaque, sealed envelopes kept by a research coordinator who has no conflicts of interest with the study team. After participants have completed baseline assessments and provided written informed consent, the responsible physician will open the corresponding envelope on-site to reveal the allocation. The statistician generating the random sequence will operate independently of the coordinator handling allocation concealment. Neither patients nor physicians will know the allocation in advance. All participants will be followed for 90 days.

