Our comprehensive efficacy evaluation employs multiple metrics: the Functional Oral Intake Scale (FOIS), fMRI-derived measures ReHo and ALFF, surface electromyography (sEMG), the Swallowing Disorders-Specific Quality of Life Questionnaire (SWAL-QOL), the National Institutes of Health Stroke Scale (NIHSS), Fiberoptic Endoscopic Evaluation of Swallowing (FEES) integrated with the Penetration-Aspiration Scale (PAS) and Yale Pharyngeal Residue Severity Rating Scale (YPR-SRS), and Patient-Reported Outcomes (PRO). Functional MRI (fMRI) serves as a superior non-invasive neuroimaging modality for dynamic neural activity monitoring (61), offering exceptional spatial resolution for mapping cerebral activation patterns across cortical and subcortical structures (thalamus, basal ganglia, cerebellum, and brainstem) (62). Crucially, fMRI captures data under near-physiological conditions, enabling investigation of spontaneous neuronal activity, functional connectivity networks, and neuroplastic changes (63). Previous research demonstrates an inverse correlation between ReHo values in swallowing-related brain regions and dysphagia severity in stroke patients (47), suggesting ReHo alterations may track neural compensation during swallowing recovery (48). Similarly, ALFF—quantifying spontaneous neural activity intensity (64)—shows treatment responsiveness (65). The SWAL-QOL is a validated assessment tool characterized by simplicity of administration, time efficiency, high reliability, and good validity (34). It provides quantitative measurement of swallowing-related quality of life, enabling clinicians to better evaluate patients’ swallowing function and dysphagia severity. The NIHSS employs standardized scoring criteria that ensure inter-rater reliability and comparability (48). Numerous studies have established the NIHSS as a simple yet effective predictive measure for neurological deficits (66–68), which can be used to forecast long-term functional recovery and guide rehabilitation planning. The objective observations from FEES are translated into quantifiable efficacy data using the Penetration-Aspiration Scale (PAS) and Yale Pharyngeal Residue Severity Rating Scale (YPR-SRS), thereby enhancing the precision of therapeutic outcome evaluation for the intervention. This study comprehensively evaluates acupuncture efficacy through four key dimensions: physiological function, cerebral activity, quality of life, and disease severity, thereby generating high-quality, internationally recognized evidence-based findings.

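### The whole-brain fMRI plan applies paired t-tests to two unpaired randomised arms, with a one-tailed correction whose rationale does not cover that contrast

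*Protocol article*

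**What the plan says.** Section 2.12.1 of the protocol article sets out the whole-brain analysis in two sentences. The first names the test: "Paired *t*-tests will be used to compare pre- and post-intervention ALFF, fALFF, ReHo, and FC values", applied "within each group (acupuncture and rehabilitation training), as well as between groups after intervention". No other test is named for the maps.

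The second gives the reason for a directional correction, "Based on prior evidence indicating direction-specific neuromodulation by acupuncture in swallowing networks", and states that the resulting maps "will be corrected using one-tailed Gaussian random field theory", at voxel p < 0.01 and cluster p < 0.05. It does not say which tail.

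The arms are described in 2.2 as "100 PSD patients to be randomly allocated in a 1:1 ratio to either the experimental group or the rehabilitation control group". Section 2.7 gives the method: stratified blocks, "with study center and baseline FOIS as stratification factors, block lengths of 4 and 6 randomly interleaved". Neither section matches individual patients.

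The rest of 2.12.1 plans a separate region-of-interest (ROI) analysis of mean ReHo and ALFF by repeated-measures ANOVA, covering change over time and differences between groups.

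**The concern.** A paired t-test needs a natural link between each observation and its partner. Scans of one patient before and after treatment have that link. Scans of an acupuncture patient and a rehabilitation patient do not. The sentence nevertheless gives both contrasts the same test.

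The one-tailed rule raises a second problem on the same map. Evidence that acupuncture pushes activity in one direction says nothing about the sign of acupuncture minus rehabilitation, because the comparator is an active treatment that the Discussion treats as the standard of care.

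Clarifying the neural mechanism is a stated objective (2.1). Only the between-arm contrast is protected by randomisation. Change within an arm cannot be separated from spontaneous recovery in patients enrolled 15 to 180 days after stroke. The whole-brain map that would support a statement about acupuncture versus rehabilitation is therefore the one with the unsuitable test. Leaving patient order and tail open also allows both to be settled after results are seen.

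**Working it through.** **Inputs.** 40 patients per arm after a 20% dropout allowance, 100 enrolled (2.7); parallel 1:1 arms (2.2); scans excluded for head motion above 2 mm or 2°, or for artifacts (2.9.2.1); voxel and cluster thresholds as above (2.12.1). The article gives no fMRI effect size or fMRI sample size, so the 0.5 and 0.8 SD effects below are assumptions.

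**1. The plan's own figure.** The only computed size is for FOIS. With difference 1.00, margin 0.39, SD 1.09, one-sided alpha 0.05 and power 0.80: n = 2 × (1.645 + 0.842)² × 1.09² / 0.61² ≈ 39.5, so 40 per arm, and 40 / 0.8 = 50. It reproduces. It is used here only as the source of n = 40 and n = 50.

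**2. Can the paired test be run?** It needs equal numbers. With 50 per arm and each scan retained independently with probability 0.8, P(equal) = Σₖ [C(50,k) 0.8ᵏ 0.2⁵⁰⁻ᵏ]² = 0.0998. As a check, the difference in completers has variance 2 × 50 × 0.8 × 0.2 = 16, so SD 4, and P(0) ≈ 1 / (4√(2π)) ≈ 0.100. The test is therefore undefined about 90% of the time under this assumption.

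**3. If numbers are equal.** The paired statistic is t = (mean A − mean B) / √(s²_D / n), with s²_D = s²_A + s²_B − 2s_AB. The numerator is the same for every ordering. The covariance s_AB is created by the ordering alone, so the p-value moves with it. In one simulated data set (40 per arm, assumed shift 0.5 SD, 3,000 re-pairings), the one-sided paired p ran from 0.009 to 0.092, with the central 95% from 0.024 to 0.072. The two-sample p was 0.046. This illustrates scatter, not bias.

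**4. Error rate and power of arbitrary pairing.** Simulation of 40,000 replicates at a single voxel, independent normal arms, n = 40, one-tailed p < 0.01:

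| | Paired | Two-sample |
|---|---|---|
| Type I error | 0.009 | 0.009 |
| Power, 0.5 SD | 43.5% | 45.0% |

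Degrees of freedom fall from 2 × 40 − 2 = 78 to 40 − 1 = 39.

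**5. One tail mapped.** Detection of an effect opposite to the chosen tail, voxel p < 0.01:

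| n per arm | Assumed effect | As written (paired, one-tailed) | Two-sample, two-tailed |
|---|---|---|---|
| 40 | 0.5 SD | about 0% | 35% |
| 40 | 0.8 SD | 0% | 82% |
| 50 | 0.5 SD | 0% | 45% |
| 50 | 0.8 SD | 0% | 91% |

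**6. Both tails each mapped one-tailed.** Voxel error is about 0.02 in place of 0.01. Cluster-level family error is 1 − 0.95² = 0.0975 if the two maps are treated as independent, and at most 0.05 + 0.05 = 0.10.

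**The case against.** The sentence may be loose drafting in a condensed article, with a two-sample test intended. The slip would probably surface at analysis, since software refuses a paired test on unequal arms. That is plausible, but the text names no other whole-brain test, so the sentence still needs correcting.

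Several stronger readings are tempting and are not supported:

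- **The between-arm map would give false positives.** A reader might infer this from calling the test wrong. Step 4 shows otherwise: type I error is held and the power loss is about 1.5 percentage points. The fault is that the test does not apply.
- **The mechanistic objective as a whole fails.** The ROI analysis uses pre-specified regions and scans at baseline, Day 15 and Day 30. It needs no pairing across arms and carries no stated one-tailed rule. Section 2.12.5 also plans mixed models or regression for secondary efficacy outcomes, and ReHo and ALFF are listed as secondary.
- **Ignoring the baseline scan is an error.** A post-treatment contrast between randomised arms is unbiased. Baseline adjustment usually buys precision, and the ROI analysis already uses the baseline scan.
- **The cited evidence gives no direction.** The Discussion uses one of the two sources cited for the one-tailed rule to say: "Previous research demonstrates an inverse correlation between ReHo values in swallowing-related brain regions and dysphagia severity in stroke patients". A reader might conclude that these sources cannot justify a tail. They are not at hand, and a source can support more than one statement. What stands is narrower: the rationale as worded is about acupuncture, not about its difference from rehabilitation.
- **Opposite effects are missed and the error rate doubles.** These are alternatives. The first follows if one tail is mapped, the second if both are, and the article does not say which.

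**Conclusion.** The point holds for the between-arm whole-brain contrast. The paired t-test is inapplicable there: undefined in most realistic outcomes, and dependent on ordering in the rest. The 10% chance of equal numbers assumes exactly 50 per arm and independent 20% loss of scans; head-motion exclusions would come on top of dropout. The one-tailed correction of that contrast has no stated justification and no stated direction. Its consequence is either near-zero detection of differences in the unmapped direction or a family error of up to about 10%. The detection figures are for a single voxel and assumed effects, not cluster-level power.

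The ROI ANOVA, the within-arm paired tests and the primary FOIS analysis are untouched by the pairing error. No fault is claimed here in the directional rule for the within-arm maps. Because fMRI is a secondary outcome, the correction should be made but does not bear on the trial's main conclusion.

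**What to change.** In 2.12.1, keep paired t-tests for within-arm change only. For the between-arm whole-brain contrast, specify one of:

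- a two-sample t-test on change maps (Day 30 minus baseline); or
- a voxelwise ANCOVA of the Day 30 map on arm, with the baseline map as covariate.

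Apply two-tailed Gaussian random field correction to that contrast, and base whole-brain claims about acupuncture versus rehabilitation on it. Record the choice before any between-arm map is computed.

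This needs no new data or scans, only a different model specification. The price is a stricter voxel threshold: with 40 per arm, |t| > 2.640 on 78 degrees of freedom, against t > 2.426 on 39 as written. In the favoured direction, at an assumed 0.5 SD, single-voxel detection by the two-sample two-tailed test is 35%, against 44% for the paired one-tailed test (n = 40). These figures give no credit for any precision gained from using the baseline scan.

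### Whole-brain maps: with random field correction at a lenient voxel p < 0.01, the stated cluster p < 0.05 is not assured unless spatial correlation is close to Gaussian-shaped

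*Protocol article*

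**What the plan says.** Section 2.12.1 (Functional imaging evaluation indicators) plans whole-brain tests to "compare pre- and post-intervention ALFF, fALFF, ReHo, and FC values within each group", and also between groups after the intervention. The resulting maps are to be "corrected using one-tailed Gaussian random field theory (voxel *p* < 0.01, cluster *p* < 0.05".

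Section 2.9.2.1 gives the processing that determines smoothness: "spatial normalization to the MNI152 template at 2 mm^3^ isotropic resolution" and "spatial smoothing will be applied using a 6 mm full-width-at-half-maximum Gaussian kernel".

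The article names no permutation or other non-parametric check and no stricter cluster-forming threshold. It reports neither an estimated smoothness nor the shape of the spatial correlation. Section 2.12.1 also plans a separate analysis of mean ReHo and ALFF in predefined regions by repeated-measures ANOVA. That analysis uses no cluster-size inference.

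**The concern.** Random field theory turns a smoothness estimate, taken from neighbouring voxels, into the cluster size that chance alone should rarely exceed. The step assumes that correlation falls off with distance in a Gaussian shape. At z = 2.33 the clusters above threshold are large, and their extent depends on correlation at distances that the neighbouring-voxel estimate does not see. If correlation has a longer tail, the cut-off is too small and chance clusters pass it. The 6 mm kernel smooths the data but does not remove such a tail, and nothing in the article shows that maps of ReHo, ALFF, fALFF or FC lack one.

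At stake is the meaning of a cluster reported as corrected p < 0.05 in the whole-brain part of the mechanistic objective. For fALFF and FC the whole-brain maps are the only planned analysis. The point concerns the error rate within one map. The number of maps, the pairing of the t-tests and the use of one tail are separate matters.

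**Working it through.** **Inputs from the article.** Voxel p < 0.01 one-tailed, so z = 2.326; cluster p < 0.05; 6 mm kernel; a 2 mm grid (read as voxel edge). Patients per arm: "After calculation, nA = nB = 40", which follows from "These parameters (μA = 1.31, μB = 0.31, σ = 1.09, α = 0.05, power = 0.8, δ = 0.39": 2 × 1.09² × (1.645 + 0.842)² / (1.00 − 0.39)² = 39.5, rounded up to 40. A within-arm paired map then has 39 degrees of freedom.

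**Assumptions, not in the article.** An ellipsoid mask of 226,845 voxels (1.81 L), the effective smoothness, and the size and shape of any long-range correlation.

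**Cut-off formula.** For smoothness F in voxels, dLh = (4 ln 2)^1.5 / F³. The expected number of clusters is Em = V · (2π)⁻² · dLh · (z² − 1) · exp(−z²/2). With β = [Γ(5/2) · Em / (V · p)]^(2/3), the cut-off k solves 1 − exp(−Em · exp(−β k^(2/3))) = 0.05.

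Example for 6 mm, where F = 3 voxels: dLh = 0.171, Em = 289.6, β = 0.3065 and k = 150 voxels. For 8 mm, Em = 122.2, β = 0.1724 and k = 303. At voxel p < 0.001 the two cut-offs are 47 and 92.

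**The plan's figure first.** With purely Gaussian correlation, 1,200 simulated Gaussian null maps per setting gave a per-map error of 1.8% (6 mm), 2.5% (8 mm) and 2.1% (10 mm). For t maps with 39 degrees of freedom at 8 mm it was 0.5% (200 maps). The stated 5% is reproduced as an upper bound, with room to spare.

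**With a long-range component added** (same mask, 1,200 Gaussian maps each; 95% Monte Carlo half-width about 1 to 2.5 points):

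| Core + long-range part (share of variance) | Voxel p < 0.01 | Voxel p < 0.001 |
|---|---|---|
| 8 mm + 3% of 20 mm Gaussian | 3.7% | 2.4% |
| 8 mm + 5% of 20 mm Gaussian | 4.2% | 2.4% |
| 8 mm + 10% of 20 mm Gaussian | 8.0% | 3.0% |
| 8 mm + 20% of 20 mm Gaussian | 13.0% | 5.5% |
| 8 mm + 30% of 20 mm Gaussian | 19.5% | 7.1% |
| 8 mm + 20% exponential (10 mm) | 10.6% | 4.1% |
| 8 mm + 30% exponential (10 mm) | 18.0% | 6.3% |
| 8 mm + 50% exponential (10 mm) | 23.9% | 9.4% |
| 8 mm + 20% exponential (15 mm) | 15.8% | 4.7% |
| 6 mm + 20% exponential (10 mm) | 25.6% | 5.7% |

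For t maps with 39 degrees of freedom (200 maps, 8 mm + 20% of 20 mm Gaussian), the error at voxel p < 0.01 was 10% (± 4).

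**Other grids, same pattern.**
- 65,256 voxels of 3 mm, 40 patients, one-sample t maps, 300 data sets per setting, 8 mm core plus a 24 mm component: 2.7%, 12.7% and 23.3% at shares of 0%, 15% and 30%. At voxel p < 0.001: 1.0%, 2.0% and 5.3%. The Monte Carlo standard error is at most 2.4 points.
- 97,096 voxels, Gaussian maps, same two components: 2.2% for pure Gaussian, 4.3% at a 5% share, 13% to 14% at 10% to 20%, and 24% at 30%. At voxel p < 0.001: 2% to 8%.

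**The case against.** The plan fixes its method, threshold, tail and smoothing in advance and contains no contradiction or wrong figure here. An unproven assumption is not one shown to fail, and the article supports no particular tail weight. Each of these statements is correct, and together they limit what can be claimed.

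A reader might infer that cluster p < 0.05 holds only if correlation is exactly Gaussian. That does not follow: the method is conservative in the Gaussian case, and a long-range share of 3% to 5% still gave about 4%.

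A reader might also take one inflated rate, such as 13% to 23%, as a property of this trial. It is not, because every such figure comes from a chosen correlation mix. The between-group map was not simulated, and the one inflated setting run as t maps on the 2 mm grid gave 10% (± 4), against 13.0% for Gaussian maps with the same mix.

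Nor do the results suggest that voxel p < 0.001 is a complete cure, since it still reached 9.4% in one setting.

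What survives is that the stated error rate depends on an unchecked assumption to which this threshold is sensitive. In every setting with a 10% or larger long-range share, voxel p < 0.01 exceeded 5% and had a higher error than voxel p < 0.001.

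**Conclusion.** The point stands as an improvement worth making, not as an error that undermines the trial. Under the plan's settings, the nominal 5% per map is met when correlation is Gaussian or nearly so. It is exceeded by a factor of about 1.6 to 5 (8% / 5% to 26% / 5%) when roughly 10% to 50% of the variance has longer range. Where this trial's maps lie in that range cannot be determined from the article. The size depends on the assumed tail and on core smoothness: the largest value, 25.6%, came from a 20% share on a 6 mm core.

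One might read this as casting doubt on the efficacy conclusion or on all the imaging evidence. The article does not support that: FOIS, the sample size and the regional ReHo and ALFF analysis do not use cluster-size inference.

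**What to change.** In section 2.12.1, replace the random field correction with permutation-based cluster inference at family-wise 0.05 per map: sign-flipping of the paired differences within each arm, and permutation of arm labels for the between-arm comparison. Use voxel p < 0.001 as the cluster-forming threshold by preference. Permutation needs no assumption about the shape of spatial correlation; sign-flipping does need differences that are symmetric under the null.

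If random field theory is kept, change the voxel threshold to p < 0.001 and state that this reduces the excess error without fully removing it.

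Make and date the change before the imaging comparisons are run. It costs wording, computing time and some sensitivity to weak, diffuse effects. No further scans, patients or visits are needed.
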